## Abstract

**Background:**

Anterior cruciate ligament (ACL) reconstruction is today’s surgical gold standard for ACL rupture. Although it provides satisfactory results, not all patients return to their previous activity level and moreover, early posttraumatic osteoarthritis is not prevented. As such, a renewed interest has emerged in ACL suture repair combined with dynamic augmentation. Compared to ACL reconstruction, the hypothesized advantages of ACL suture repair are earlier return to sports, reduction of early posttraumatic osteoarthritis and preservation of the patient’s native ACL tissue and proprioceptive envelope of the knee. In recent literature, ACL suture repair combined with dynamic augmentation tends to be at least equally effective compared to ACL reconstruction, but no randomized comparative study has yet been conducted.

**Methods/design:**

This study is a prospective, stratified, block randomized controlled trial. Forty-eight patients with an ACL rupture will be assigned to either a suture repair group with dynamic augmentation and microfracture of the femoral notch, or an ACL reconstruction group with autologous semitendinosis graft and all-inside technique. The primary objective is to investigate the hypothesis that suture repair of a ruptured ACL results in at least equal effectiveness compared with an ACL reconstruction in terms of patient self-reported outcomes (IKDC 2000 subjective scale) 1 year postoperatively. Secondary objectives are to evaluate patient self-reported outcomes (IKDC 2000, KOOS, Tegner, VAS), re-rupture rate, rehabilitation time required for return to daily and sports activities, achieved levels of sports activity, clinimetrics (Rolimeter, LSI, Isoforce) and development of osteoarthritis, at short term (6 weeks, 3, 6 and 9 months and 1 year), midterm (2 and 5 years) and long term (10 years) postoperatively.

**Discussion:**

A renewed interest has emerged in ACL suture repair combined with dynamic augmentation in the treatment of ACL rupture. Recent cohort studies show good short- and midterm results for this technique. This randomized controlled trial has been designed to compare the outcome of suture repair of a ruptured ACL, combined with DIS as well as microfracture of the femoral notch, with ACL reconstruction using autologous semitendinosus.

**Trial registration:**

Clinical Trials Register NCT02310854 (retrospectively registered on December 1st, 2014).

## Background

Rupture of the anterior cruciate ligament (ACL) is one of the most common injuries of the knee [1]. Reported incidence varies between 0,3 and 0,8 per 1000 [2, 3] and most patients with ACL ruptures are young sportively active individuals (males 15–34 years; females 14–21 years) [4]. ACL rupture is a serious injury of the knee with high probability of the occurrence of dynamic instability, accompanying lesions and early post-traumatic osteoarthritis [5–10].

The treatment of ACL ruptures is aimed at achieving return to previous activity levels by resolving the instability of the affected knee, and preventing the development of post-traumatic osteoarthritis. The surgical gold standard is ACL reconstruction [11]. However, Biau et al. [12] concluded in a meta-analysis that only 40% of patients return to their previous activity levels after ACL reconstruction surgery. Moreover, the incidence of re-rupture of the reconstructed ACL is 3–22% within 2 years after surgery [13–15] and the risk of early posttraumatic osteoarthritis is still present [8–10].

In order to optimize the clinical results after ACL rupture, a renewed interest has emerged in ACL suture repair. In contemporary repair techniques, the sutured ACL is augmented with a strong, small diameter braid. In a biomechanical study, Kohl et al. demonstrated that, in contrast to static augmentation, dynamic augmentation is able to restore anterior-posterior stability of the knee directly postoperative as well as after cyclic loading [16]. In a pilot study, ACL suture repair combined with dynamic augmentation and microfracture in the femoral notch resulted in satisfactory clinical and radiological healing of the torn ACL at one and 5-year follow-up [17, 18]. Also, in three prospective cohort studies, two with one-year follow-up in 26 and 45 patients and one with 2 years follow-up in 69 (of 278) patients, ACL repair with dynamic augmentation provided successful functional recovery and patient self-reported outcomes [19–21]. Moreover, patients could return to their previous level of sports within 5 months after surgery [17, 20]. In terms of complications, the failure rate seems comparable to the re-rupture rate of ACL reconstruction. The pilot study of Eggli showed one failure in 10 patients after a 2 year follow-up and two failures in 10 patients after a 5 year follow-up [17, 18]. A larger cohort study of Henle showed 4% failure rate in 69 (of 278) patients after 2 years follow-up [20].

Ergo, ACL suture repair with dynamic augmentation seems to be a promising technique. However, to date no randomized comparative study has been conducted in which ACL suture repair with dynamic augmentation is compared with the gold surgical standard, ACL reconstruction. This study aims to investigate the hypothesis that suture repair of a ruptured ACL, combined with dynamic augmentation as well as microfracture of the femoral notch, will result in at least equal effectiveness compared with ACL reconstruction using autologous semitendinosus in terms of patient self-reported outcomes (IKDC 2000 subjective scale) 1 year postoperatively.

## Methods

### Study design

This study is a Medical Ethical Committee approved, (Medical Ethics Committee ‘Twente’, reference number NL50116.044.14/P1426) prospective, stratified and block randomized controlled trial: patients will be allocated to undergo either ACL suture repair or ACL reconstruction. The study will be conducted at the Centre for Orthopaedic Surgery OCON, Hengelo, The Netherlands.

Patients will be recruited at the outpatient department of OCON and informed about the study by their orthopaedic surgeon. After 2–3 days of reflection, an independent investigator will check eligibility and obtain informed consent. One orthopaedic surgeon will operate all patients. Blinding of the surgeon, physiotherapist who will conduct clinimetrics and patient is not used due to practical reasons. All patients will receive identical rehabilitation after surgery, apart from bracing in extension lock for the first 5 days postoperative in the repair group; the standard nationally used physiotherapy protocol regarding ACL reconstruction is given to the patient and their own physiotherapist. Patients will be followed-up in the outpatient clinic preoperatively as well as 6 weeks, 3, 6, 9 months, 1, 2, 5 and 10 years postoperatively (Fig. 1), where all the outcome measurements will be conducted. With weekly data management patients will be contacted in case of no show in order to minimize loss to follow-up. Protocol modifications will be communicated via amendments according to the guidelines of the Medical Ethical Committee.

**Fig. 1 Fig1:**
[figure not shown]
Flowchart of patient inclusion

### Study sample

Patients eligible for enrolment in this study are sportively active patients between 18 and 30 years with a proven primary ACL rupture, confirmed by means of history, physical examination and MRI, for whom an indication for ACL reconstruction surgery exists and who can undergo surgery within 21 days of injury. Exclusion criteria are concomitant large meniscal injury needing repair, cartilage injury requiring surgical intervention or ligamentous lesions of the ipsilateral knee, pre-injury Tegner score below 5, history of knee surgery of the ipsilateral knee, pre-existing significant malalignment of the ipsilateral knee, hypersensitivity to cobalt, chromium or nickel, muscular, neurological or vascular abnormalities, osteoarthritis, use of prednisone or cytostatics, tendency to form excessive scar tissue, pregnancy, osteoporosis or infection.

Patients can withdraw from the study at any time. They will receive appropriate treatment according to standard-care.

### Intervention

#### ACL suture repair

ACL suture repair will be performed within 21 days after injury. The dynamic intraligamentary stabilisation (DIS) technique will be used (Ligamys, Mathys Medical, Bettlach, Switzerland). The procedure is started with standard arthroscopy to assess all compartments for concomitant injury. When a patient meets one of the exclusion criteria, they will be excluded from the study. Patients will receive further standard care including ACL reconstruction after meeting the Millet criteria. Otherwise, the procedure will be continued and the ACL rupture type will be classified. The tibial attachment of the ACL is identified using an intra-articular guide. A guide wire is overdrilled in the metaphysis and the monoblock is screwed in place. A suture to secure the ACL remnant is inserted through the screw and passed through the ligament and pulled through the femur. The femoral attachment is then marked using a guide from the anteromedial portal. A polyethylene wire will be pulled distally through the femur towards proximal tibia. The wire is stabilized at the femoral position with a cortical suspension button. The polyethylene wire is pulled through the tibia and tightened before final tension is applied. The procedure will be completed by microfracture of the femoral attachment.

Removal of the Ligamys spring will take place in day care, no earlier than after recording of the primary outcome measure 1 year after surgery. The previous anteromedial incision will be used.

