#### ACL reconstruction

ACL reconstruction will be performed when the patient meets the Millett criteria [22], usually approximately 6 weeks after injury. If necessary, additional physiotherapy will be given and patients will be rescheduled for a retest. In that case, the measurements of the retest where the Millet criteria are met will be used as baseline measurement during the study. An all-inside technique (Arthrex, Naples, Florida, USA) will be used. The semitendinosus tendon from the ipsilateral leg will be harvested and quadrupled. A standard arthroscopy will be performed for diagnosis and treatment of concomitant injuries and evaluation of ACL rupture morphology. When a patient meets one of the exclusion criteria, he will be excluded from the study, but the surgical procedure will be continued. ACL rupture will be classified. After removing ACL remnants, the tibial and femoral tunnel will be prepared. The graft will be positioned in the femoral tunnel first and fixed with a cortical suspension button with variable loop length. After, the graft will be placed in the tibial tunnel and fixed with a cortical suspension button, with the knee in 0 degrees of extension while anterior translation of tibia in relation to femur is eliminated. Positioning and tension of the graft will be verified under vision, and if necessary, the graft will be tightened.

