### Randomization

After inclusion, patients will be randomized into an experimental group (repair) or a control group (reconstruction), in blocks with varying sizes (*N* = 2 and *N* = 4) by an independent investigator with PASS (Power Analyses and Sample Size Software; rand.exe version 6.0). The extent of physical activity in daily life poses a potential risk to repair/graft failure. To make sure both groups have an equal risk of failure, patients will be stratified based on physical activity level using the Tegner score (moderate: Tegner 5-7; high: Tegner 8-10) [27, 28].

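### Randomised patients leave the study on an unblinded arthroscopic finding made at different times after injury in the two arms, so the groups kept for the 1-year comparison may be selected differently

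*Protocol article*

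**What the plan says.** All references are to the protocol article.

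- **Randomization:** "After inclusion, patients will be randomized into an experimental group (repair) or a control group (reconstruction"). Allocation must precede surgery, because the arm decides when surgery takes place.
- **Study sample:** the criteria that arthroscopy can reveal are these: "Exclusion criteria are concomitant large meniscal injury needing repair, cartilage injury requiring surgical intervention or ligamentous lesions of the ipsilateral knee".
- **Timing, repair arm:** "ACL suture repair will be performed within 21 days after injury".
- **Timing, reconstruction arm:** "ACL reconstruction will be performed when the patient meets the Millett criteria [22], usually approximately 6 weeks after injury". It is later still if a retest is needed.
- **Rule, repair arm:** "When a patient meets one of the exclusion criteria, they will be excluded from the study". The repair is then not done: "Patients will receive further standard care including ACL reconstruction after meeting the Millet criteria".
- **Rule, reconstruction arm:** "When a patient meets one of the exclusion criteria, he will be excluded from the study, but the surgical procedure will be continued".
- **Study design:** a single surgeon operates on everyone, and "Blinding of the surgeon, physiotherapist who will conduct clinimetrics and patient is not used due to practical reasons".
- **Sample size determination:** 20 per group, raised to 24 for a 20% loss to follow-up. Arthroscopic exclusions are not mentioned there.

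The text does not say that patients excluded at arthroscopy continue to complete the IKDC.

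**The concern.** Removing patients after randomisation can be harmless if it rests on a fact fixed before randomisation and is judged blind and in the same way in both arms. None of these safeguards is stated here.

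The surgeon knows the arm. Several criteria need judgement: whether a meniscal injury is large and needs repair, and whether a cartilage injury needs surgery. In the reconstruction arm the knee is inspected some weeks later, so a lesion may have arisen, worsened or settled in the meantime. An exclusion there can therefore be a consequence of allocation itself.

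What is at stake is the primary non-inferiority comparison of the 1-year IKDC. The loss cannot be repaired at analysis: if excluded patients leave follow-up, no analysis plan can recover 1-year scores that were never collected.

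**Working it through.** **1. The plan's own figure.** Inputs from Sample size determination: margin 10, SD 9, power 90%, alpha 5% (sidedness not stated), assumed true difference 0.

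n = 2 × 9² × (1.960 + 1.282)² / 10² = 17.02, so 18 per group at one-sided 2.5%. With the noncentral t it is 19. The stated 20 reproduces within 2. At one-sided 5% the result is 14 or 15, which does not match. The calculations below therefore take one-sided 2.5% as an assumption. The point exposes no arithmetic error in the 20.

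**2. When does exclusion bias the comparison?** The documents give no exclusion rate, so every rate here is assumed. Let a fraction p of each arm have a relevant concomitant injury that lowers the IKDC by D points, and let a fraction e of the arm, all of them injured, be excluded. The retained arm mean is then lowered by D(p − e)/(1 − e). Take p = 25%.

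| Excluded, repair | Excluded, reconstruction | Shift (repair minus reconstruction), D = 10 | D = 15 |
|---|---|---|---|
| 10% | 10% | 0 | 0 |
| 10% | 20% | −1.0 | −1.6 |
| 5% | 20% | −1.5 | −2.2 |
| 20% | 10% | +1.0 | +1.6 |

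First row: 10 × 0.15/0.90 = 1.67 in both arms, difference 0. Second row, D = 10: −1.67 + 10 × 0.05/0.80 = −1.67 + 0.62 = −1.0. The sign follows whichever arm loses more patients.

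**3. Effect on the type I error.** Take 20 evaluable per group and net shifts b of 0.75 and 2 points, the order of size found in step 2. SE = 9 × √(2/20) = 2.846, and the critical t on 38 degrees of freedom is 2.024. The type I error is the probability that a noncentral t with noncentrality b/SE exceeds 2.024.

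| Shift b | b/SE | Type I error |
|---|---|---|
| +0.75 (favours repair) | 0.264 | 4.4% |
| +2 | 0.703 | 10.1% |
| −0.75 (favours reconstruction) | −0.264 | 1.3% |
| −2 | −0.703 | 0.4% |

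**4. Effect on numbers.** With no arthroscopic exclusion, 24 × 0.8 = 19.2 per group, already just under 20. With 10% excluded and not replaced (both assumed), 24 × 0.9 × 0.8 = 17.3. At n = 17 the noncentral-t power is 88% at one-sided 2.5%, or 94% at one-sided 5%.

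**The case against.** Several counter-arguments have force.

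- **The direction is unknown.** A reader might infer that the rule favours repair and inflates the type I error to about 10%. The documents do not support this. If the longer wait produces more lesions in the reconstruction arm, poorer patients leave the control group, its mean rises and the bias runs against repair. That is conservative for a non-inferiority claim. This stands, and is why both signs are shown.
- **Few patients may be affected.** Baseline MRI is required and an independent investigator checks eligibility before surgery, so arthroscopy finds only what screening missed or what arose later. This also stands. It limits the likely size but leaves the mechanism in place.
- **The operation after exclusion differs by arm.** A reader might see this as a source of bias. It is not one: both kinds of patient leave the study, so what they receive next cannot alter the retained groups. Only timing and unblinded judgement can select differently.
- **The power loss is modest and conditional.** It depends on an assumed exclusion rate, on the sidedness and on no replacement. The article does not say whether excluded patients are replaced, and its flowchart is not shown.
- **Analysis sets may be defined in the full protocol or analysis plan.** That is true, and the absence of a named set from the article is not the point. The point is the stated rule that takes randomised patients out of the study.
- **An as-randomised analysis has its own weakness.** Excluded repair patients go on to reconstruction, which pulls the arms together and can favour non-inferiority. This stands, and is why one analysis set alone will not do.

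**Conclusion.** The point holds as a risk created by a stated rule. Patients are removed after randomisation, by an unblinded judgement, at arm-dependent times after injury, and nothing in the text keeps them in follow-up. The primary comparison therefore loses part of the protection of randomisation.

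To say that the randomisation is broken outright would go too far, since equal exclusion of like patients causes no bias. The error rates and power figures above illustrate the possible scale under assumed shifts and exclusion rates; they are not estimates for this trial. The reduction in numbers is secondary. What matters is that the rule must be changed while follow-up data can still be collected.

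**What to change.** Leave the surgical management under ACL suture repair and ACL reconstruction as written. Change only the words that remove these patients from the study:

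1. Patients with an exclusion criterion found at arthroscopy stay in follow-up and complete at least the IKDC at the Table 1 visits.
2. The primary analysis includes all randomised patients as allocated. The set without arthroscopic exclusions is a supporting per-protocol analysis, and both must be consistent with non-inferiority before it is claimed.
3. Arthroscopic exclusions are reported by arm, with the reason.
4. One time origin is stated for the 1-year IKDC of patients who do not receive the allocated operation, since the endpoint is currently counted from surgery.

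The cost is an amendment plus a few extra questionnaires and visits. The downside is some dilution in the as-randomised analysis, because excluded repair patients go on to reconstruction. The per-protocol set carries the selection described above, so neither analysis is sufficient alone and both should be shown.

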#### ACL reconstruction

ACL reconstruction will be performed when the patient meets the Millett criteria [22], usually approximately 6 weeks after injury. If necessary, additional physiotherapy will be given and patients will be rescheduled for a retest. In that case, the measurements of the retest where the Millet criteria are met will be used as baseline measurement during the study. An all-inside technique (Arthrex, Naples, Florida, USA) will be used. The semitendinosus tendon from the ipsilateral leg will be harvested and quadrupled. A standard arthroscopy will be performed for diagnosis and treatment of concomitant injuries and evaluation of ACL rupture morphology. When a patient meets one of the exclusion criteria, he will be excluded from the study, but the surgical procedure will be continued. ACL rupture will be classified. After removing ACL remnants, the tibial and femoral tunnel will be prepared. The graft will be positioned in the femoral tunnel first and fixed with a cortical suspension button with variable loop length. After, the graft will be placed in the tibial tunnel and fixed with a cortical suspension button, with the knee in 0 degrees of extension while anterior translation of tibia in relation to femur is eliminated. Positioning and tension of the graft will be verified under vision, and if necessary, the graft will be tightened.

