#### Primary study parameter

Differences between IKDC 2000 at baseline and one-year post-operative will be determined for each group, as well as differences between the groups at each follow-up. In case of clinically meaningful differences between groups (> 10 points on the IKDC2000), the non-inferiority hypothesis will be rejected. In case of non-inferiority, superiority analyses will be conducted. For normally distributed data mixed models analyses for repeated measures will be used. In case of non-normally distributed data, the Friedman test for differences within groups, and Mann-Whitney Y test for differences between groups, will be used. A distinction will be made between short term (6 weeks, 3, 6, 9 months and 1 year), mid-term (2 and 5 year) and long-term (10 year) postoperative outcomes.

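### The study baseline falls at different stages of recovery in the two arms, so baseline scores and per-group changes in IKDC are not comparable; the unadjusted 1-year comparison is unaffected

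*Protocol article*

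**What the plan says.** **Repair arm.** Under ACL suture repair: "ACL suture repair will be performed within 21 days after injury". Study design places the first assessment before surgery in both arms: "Patients will be followed-up in the outpatient clinic preoperatively as well as 6 weeks, 3, 6, 9 months, 1, 2, 5 and 10 years postoperatively". The repair baseline must therefore fall within 21 days of injury.

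**Reconstruction arm.** Under ACL reconstruction: "ACL reconstruction will be performed when the patient meets the Millett criteria [22], usually approximately 6 weeks after injury". Patients who do not meet the criteria follow another path: "If necessary, additional physiotherapy will be given and patients will be rescheduled for a retest". For them, "the measurements of the retest where the Millet criteria are met will be used as baseline measurement during the study".

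**Randomisation.** Under Randomization, allocation follows inclusion. Study sample requires that a patient can undergo surgery within 21 days of injury.

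**Endpoint and analysis.** Main study parameter/endpoint names the IKDC Subjective score 1 year after surgery. The analysis section, Primary study parameter, says: "Differences between IKDC 2000 at baseline and one-year post-operative will be determined for each group, as well as differences between the groups at each follow-up". It names mixed models for repeated measures and does not say how baseline enters them. Secondary study parameters (Statistics) applies the same methods to KOOS, Tegner, laxity, strength and other outcomes. Descriptive statistics plans tests of baseline characteristics between the randomised groups.

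**The concern.** A baseline supports a comparison between randomised arms only if it is measured before allocation, or at least in the same way and at the same stage in both arms. Here the assigned arm determines when it is measured, and in one arm a recovery test decides whether a measurement counts. Two patients with the same course after injury and the same 1-year score could show different changes only because one baseline was recorded early and the other after weeks of recovery.

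If early scores are lower, as is plausible, the early recovery counts as improvement in the repair arm but lies before baseline in the reconstruction arm. The error would favour the experimental arm, which is the harmful direction in a non-inferiority trial. Baseline tests of functional scores would also reflect timing rather than chance imbalance.

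**Working it through.** **1. Timing.** The latest repair surgery is on day 21. The usual reconstruction surgery is at about 6 × 7 = 42 days. The surgeries are thus about 42 − 21 = 21 days apart, or more when repair is done earlier or reconstruction waits for a retest. Baseline precedes surgery in both arms. The rule that the passed test is the baseline is explicit for retested patients and implied for those who pass first time.

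**2. The plan's own figure.** Sample size determination gives SD 9, margin 10, power 90%, alpha 5% and 20 patients per group. With a one-sided 2.5% level (the sidedness is not stated) and no true difference:

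n = 2 × 9² × (1.960 + 1.282)² / 10² = 17.02, so 18 per group; the t-based calculation gives 19.

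The stated 20 is reproduced to within two patients. SD 9 and 20 per group are used below.

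**3. Size of the shift.** Let s be the amount by which the repair baseline is lower purely through timing. The documents give no value, so s is assumed to be 5, 10 or 20 points. With b the weight given to baseline, the contrast (repair minus reconstruction) moves towards repair by b × s:

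- unadjusted 1-year score: b = 0;
- baseline-adjusted: b = within-arm slope, assumed 0.3 to 0.7 (equal to the correlation if the SDs are equal);
- change score: b = 1.

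| s (assumed) | Unadjusted 1-year | Adjusted, slope 0.3 to 0.7 | Change score | Change-score shift / margin 10 |
|---|---|---|---|---|
| 5 | 0 | 1.5 to 3.5 | 5 | 50% |
| 10 | 0 | 3 to 7 | 10 | 100% |
| 20 | 0 | 6 to 14 | 20 | 200% |

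**4. Check by simulation.** 3,000 trials were run with 20 per arm, SD 9, correlation 0.5 and a true repair deficit of 10 points. Mean estimates were:

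- s = 0: about −10 by all three methods;
- s = 10: unadjusted −9.94, adjusted −4.94, change +0.07;
- s = 20: unadjusted −9.99, adjusted +0.03, change +9.92.

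**5. What this would do to a non-inferiority test, if one were run on these scales.** With the true deficit equal to the margin, the chance of wrongly declaring non-inferiority is 1 − Φ(1.96 − b·s/SE), where SE = √[81 × (1 + b² − 2bρ) × 2/20] and ρ = 0.5.

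- Change score: SE = √8.1 = 2.85.
- Adjusted, b = 0.5: SE = √6.075 = 2.46.

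| s (assumed) | Change score | Adjusted |
|---|---|---|
| 5 | 42% | 17% |
| 10 | 94% | 53% |
| 20 | over 99% | 98% |

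The unadjusted test stays at the nominal 2.5%. The adjusted figures are approximate because they ignore the extra variance from the baseline imbalance between arms.

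**The case against.** A reader might infer that the trial's primary non-inferiority comparison is itself biased towards repair. The documents do not support that. The endpoint is the score at 1 year, and the 10-point rule concerns a difference between groups. The sentence on change from baseline describes a quantity within each group and places the between-group comparison at each follow-up. No between-group test of change is specified, and no baseline covariate is named. A mixed model with baseline means free in each arm also gives an undistorted 1-year contrast. How baseline enters the model is commonly left to an analysis plan, which is not shown, so that silence is not a fault. All of this stands, and it limits the point to changes set side by side and to analyses that adjust for this baseline.

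The size and direction of the shift are also assumed, since there are no preoperative IKDC values. That stands too, although the waiting period, physiotherapy and retest presuppose some recovery. For other measures the case is weaker. The article does not say whether the baseline Tegner score is the pre-injury level, which timing would not alter, and nothing indicates which way laxity would move.

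Finally, a preoperative measurement is a reasonable reference for describing change after surgery within one arm. It does not follow that the same measurement can serve as the study baseline across arms, which is the use the retest rule gives it.

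**Conclusion.** The point holds in limited form and should be fixed. The stated rules put the baseline within 21 days of injury in one arm. In the other they put it after randomisation, at a passed recovery test. Baseline functional scores and the per-group baseline-to-1-year IKDC changes are therefore not comparable between arms.

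Comparing those changes would favour repair by the full timing shift, which is 50% to 200% of the margin if the shift is 5 to 20 points. Adjusting for this baseline would favour repair by 0.3 to 0.7 of the shift at the assumed slopes, and by nothing if the slope is zero. These figures assume lower scores early after injury; the false-declaration rates also assume a correlation of 0.5.

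The unadjusted 1-year difference, which the article also plans, is unaffected, so the documents do not show a defect in the primary comparison as stated.

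**What to change.** 1. Collect IKDC and the other baseline questionnaires at inclusion, before randomisation, in both arms, and define these as the study baseline.
2. Keep the measurements from the Millett test as a separate preoperative record that does not serve as the study baseline.
3. State that non-inferiority is decided on the between-group difference in 1-year IKDC, adjusted only for the pre-randomisation value, or unadjusted if patients already enrolled lack it.
4. Label changes from the arm-specific preoperative measurement as within-group description, not for comparison between arms.

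The cost is one extra questionnaire set at an existing outpatient visit, plus analysis wording. Surgical timing and clinical rules do not change. A pre-randomisation score cannot be recovered later, so the change is worth most if made while patients are still being enrolled.
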